### Interventions

After recruitment, researchers will evaluate the cardiopulmonary function of participants, educate them about cardiac rehabilitation, and then give them exercise prescription for CR. All the participants will complete 36 CR sessions in CR Center of Fuwai Hospital within 12 weeks.

Participants allocated to the conventional exercise group will receive a closely supervised, group-format aerobic exercise program recommended by current guidelines [6, 26] in the Cardiac Rehabilitation Center for 3 months. The program includes education on diet and nutrition, medication, smoking cessation, physical and mental health, and so on.

In addition to conventional exercise described above, each patient in the intervention group will also receive *Baduanjin* exercise training. Given the low-activity tolerance of CHF patients, we performed with a modified version of *Baduanjin* exercise, in which the difficult movements for CHF patient are removed according to the “Health Qigong *Baduanjin* Standard” enacted by the General Administration of Sports in 2003 and some movements beneficial to cardiopulmonary function for CHF patients are added. They will perform standard training guided by specific *Baduanjin* exercise instructors twice a week, for a total of 12 weeks. Each training session lasts for 45 min, including breathing techniques and mild warm-up (15 min), *Baduanjin* movement (25 min), and relaxation at the end (5 min).

Researchers will record the subjects’ heart rate and blood pressure before and after training. During the training, exercise intensity will be assessed by the Borg Rating of Perceived Exertion Scale (RPE Scale) [27], which is a frequently used quantitative measure of perceived exertion during exercise. A perceived exertion of 12 or 13, which means “somewhat hard,” is considered the best and at which condition the subjects’ heart rate will be recorded. Subjects will be encouraged to practice B*aduanjin* or conventional exercise at least 30 min a day at home followed the instructional DVD until finishing the follow-up at 6 months. The duration of intervention and followed-up is illustrated in Fig. 2.

**Fig. 2 Fig2:**
[figure not shown]
The duration of intervention and followed-up

### Concomitant treatment

Participants in both groups will continue routine medications, such as anti-platelet and anti-coagulant drugs, angiotensin-converting enzyme (ACE) inhibitors or beta-adrenergic blockers, according to patients’ conditions and maintain their usual treatment visits throughout the study. The doses of ACE inhibitors or angiotensin-receptor blockers and beta-blockers should be gradually increased to target dose whenever possible. All procedures as well as medication prescription will be determined by physicians following the clinical guidelines [28, 29]. The date and reasons of any medical therapy change will be recorded in the case report form (CRF).

### Study outcome measures

The primary outcome is changes in 6-min walking distance assessed by the 6-min Walk Test (6MWT) from baseline to the end of the 12-week intervention. The 6MWT is a quick, safe, and well-tolerated measure that can reflect the functional status in patient with cardiovascular disease.

Secondary outcome includes changes in VO_2_ peak, PVO_2_ and VAT, and VE/ VCO_2_ slope in the cardiopulmonary exercise test (CPET) after the 12-week intervention. CPET is an objective method being increasingly used in a wide spectrum of clinical practice for assessing the functional capacity of CHF patient and has become an important tool to evaluate exercise capacity and predict outcome in patients with heart failure [20].

LVEDVi and LVEF are also to be assessed using echocardiography at baseline and at the end of the 12-week intervention.

MLHFQ, the most widely used scale for assessing the quality of life (QOL) in HF patients, will be used to assess how these two kinds of CR program will affect quality of life of patient with CHF from physical, emotional, social, and mental dimensions.

The serum level of NT-proBNP, an established biomarker that can reflect the cardiac function and stability of heart failure, and hs-CRP, a factor that is independently associated with adverse cardiovascular events, will be also evaluated at baseline and at the end of the 12-week intervention.

MACE, including cardiac death, nonfatal myocardial infarction, documented unstable angina requiring revascularization (bypass surgery or percutaneous coronary intervention), all-cause mortality, re-admission for acute coronary syndrome, heart failure, malignant supraventricular and ventricular arrhythmias influencing hemodynamics, ischemic stroke, and other thromboembolic events during the 6 months’ follow-up will also be recorded.

NYHA classification and the HRV mainly including the SDANN Index and SDNN Index will also be evaluated at baseline and at the end of the 12-week intervention. Table 2 indicates the data to be collected at each phase of the study.

**Table 2 Tab2:** Study procedures of the BEAR trial

	Phase I: Screening	Phase II: Baseline	Phase III: Month 3	Phase IV: Month 6
Inclusion/exclusion criteria	√			
Signed informed consent	√			
Randomization and allocation	√			
Medical history		√		
Basic characteristic		√	√	√
Physical examination		√	√	√
Medications		√	√	√
Laboratory tests		√	√	
6-min Walk Test		√	√	
Cardiopulmonary exercise test		√	√	
Echocardiography		√	√	
MLHFQ		√	√	√
NYHA classification		√	√	
Incidence of MACE			√	√
Adverse events			√	√
Adherence			√	√
Overall evaluation				√

*MACE* major adverse cardiac events, *MLHFQ* Minnesota Living with Heart Failure Questionnaire, *NYHA* New York Heart Association

### Safety/security assurance

Study participants are monitored weekly during the study intervention for the occurrence of adverse events defined as any undesirable experience. All adverse events during the study will be recorded on an adverse event CRF and will be evaluated for relevance to the intervention. Adverse events will also be reported to the Human Research Committee promptly in accordance with guidelines.

We will strictly follow recommendations from the consensus document of the Heart Failure Association, the European Association for Cardiovascular Prevention and Rehabilitation as well as the exercise standard for testing and training in the consensus from the American Heart Association [30, 31] when conducting Cardiopulmonary exercise testing (CPET). When screening patients, only those eligible and able to finish the test will undergo Cardiopulmonary exercise testing (CPET). Moreover, for enrolled patients meeting the rehabilitation training standard, we stratify them according to the degree of motion risk, and then arrange proper exercise intensity and time according to the risk stratification. Before CR exercise, researchers will educate patients on CHF rehabilitation exercises including training contraindication and notes that should be paid attention to during conventional CR exercise and *Baduanjin* exercise. Moreover, the CR Center of Fuwai Hospital has perfect rescue equipment and we created a thorough contingency plan and rescue procedure for cardiovascular events before the research began. Once adverse events occur during exercise, researchers will immediately start the contingency plan in case of fatal outcomes.

### Data management

The GCP Clinical Center of Xiyuan Hospital will be responsible for randomizing subjects into different groups, monitoring research progress, managing the data, and performing statistical analyses. All investigators involved in data management and analysis will be blinded to treatment allocation. All patient data will be recorded by trained clinical researchers using a standardized, preprinted, and paper CRF. If complete, the CRF will be locked for further revision in preparation for data entry. All CRFs are kept in a secure and lock-protected location. In accordance with our study protocol, extensive procedures are in place to ensure quality control of data entry, missing data minimization, and subject confidentiality. The statistician reviews the database to ensure accurate data collection and correct data export for future analyses. For example, at the GCP Clinical Center, a data manager uninvolved with subsequent data analysis will be responsible for overseeing data entry; to ensure the reliability of the recorded data, two investigators will independently input a copy of the CRF data into a database. A third individual will check the two independently completed database to ensure that they are identical and accurately represented. If the database records are not identical, the data in question will be confirmed from the original CRF, and if any data in the CRF is unclear, the data manager will submit a clarification form to the principal investigator of the study, who will then issue a request for the clinical researchers to resolve it as soon as possible. After blindly checking the database and confirming the accuracy and correctness of the database, we will lock the database for further analysis.

### Statistical analysis

Continuous variables will be presented as the mean ± standard deviation (SD), median or interquartile range (IQR), and categorical variables as frequencies or percentages. Comparability of the baseline data between the two groups will be assessed using a two-sample Student’s *t* test for continuous variables, and the chi-square test or Wilcoxon test for categorical variables. Questionnaire score data, known as non-normally distributed data, will be transformed or analyzed with a nonparametric test.

Analysis of the primary outcome will be conducted according to the intention-to-treat (ITT) principle. The ITT set includes all patients randomized, and the per-protocol set consists of all patients with no major deviation from the protocol and with an adherence rate of 80% or higher at the end of the study. The safety set consists of ITT patients excluding those who receive no CR program or who have no safety record after randomization. We will assess the effect of any missing data on the final results by sensitivity analysis. Dropouts will be included in the analysis by modern imputation methods for missing data.

For all analyses, all tests will be two tailed and a statistical probability of < 0.05 is considered statistically significant. All analyses will be conducted using SPSS 18.0 software (SPSS, Inc., Chicago, IL, USA), unless otherwise noted.

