## Methods/design

### Trial oversight

*Baduanjin* exercise for patients with ischemic heart failure in phase-II cardiac rehabilitation (BEAR) trial is a single-center, parallel-design, prospective RCT, and will be conducted at Fuwai Hospital, Chinese Academy of Medical Sciences, China. One hundred and twenty participants are to be recruited and the recruitment is scheduled to begin in May 2017. Participants will be randomly assigned in a 1: 1 ratio to *Baduanjin* exercise combined with conventional exercise (experiment group) or conventional exercise alone (control group) training for 12 weeks. Outcomes will be measured at baseline, 3 months and 6 months by researchers blinded to group allocation. Change in walking distance in the 6-min Walk Test (6MWT) [18, 19] from baseline to 6 months will be served as the primary outcome parameter, whereas the change in exercise capacity index, such as peak oxygen uptake (VO_2_ peak), ventilatory anerobic threshold (VAT), the minute ventilation to carbon dioxide production relationship (VE/VCO_2_ slope) determined by cardiopulmonary exercise test (CPET) [20, 21], LV end-diastolic volume index (LVEDVi), and left ventricular ejection fraction (LVEF) assessed using echocardiography, scores assessed using life quality of the Minnesota Living with Heart Failure Questionnaire (MLHFQ) [22], amino-terminal pro-brain natriuretic peptide (NT-proBNP), high-sensitivity C-reactive protein (hs-CRP), heart rate variability (HRV), major adverse cardiovascular events (MACE), and NYHA classification, will serve as secondary outcome parameters. The study protocol and consent documents have been reviewed and approved by the Ethics Committee of Xiyuan Hospital of China Academy of Chinese Medical Sciences (reference number: 2013XL063–1). If there is any amendment to the protocol, approval must be again sought from the Ethics Committee. The study has been registered at ClinicalTrials.gov (NCT03229681), and the trial will be performed in accordance with the principles of the Declaration of Helsinki and Good Clinical Practice guidelines.

Study flow of the trial is illustrated in Fig. 1 and described in detail below according to the Consolidated Standards of Reporting Trials (CONSORT) 2010 Statement [23] and the Standard Protocol Items: Recommendations for Interventional Trials (SPIRIT) Checklist (see Additional file 1).

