### Sample size calculation

Sample size is calculated, based on the 6MWT, according to the following superiority test formula:$$ {n}_c=\frac{\left(1+\frac{1}{k}\right){\left({\mu}_{1-\alpha }+{\mu}_{1-\beta}\right)}^2{\sigma}^2}{{\left[\left({x}_t-{x}_c\right)-\varDelta \right]}^2}, $$

*n*_*t*_ = *kn*_*c*_, The patients’ numbers were arranged in equal proportion (*k* = 1), a superiority one-sided test was employed. According to result of a previous study [32], *x*_t_ = 512.5, *x*_c_ = 436.2, *δ*_t_ = 50.2, *δ*_c_ = 49.8, *δ* is the estimated standard difference calculated as 50.0, and *Δ* = 0.9, *δ* = 45.0. Setting a type I error rate of alpha at 0.05, *μ*_1-a_= 1.64, and setting a type II error rate of beta at 0.1 (a power of 90%), *μ*_1-β_ = 1.282, the calculated sample size of each group is around 49. Assuming conservatively that 20% may be lost to follow-up within 6 months, the total sample size needed to detect this difference at a 5% level of significance with a power of 90% is 118 patients. For our study, we decided to recruit 120 patients for the convenience of randomization.

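### Prespecify the 6MWT primary analysis as ANCOVA on baseline 6MWT, and replace the planned baseline significance tests with a descriptive table

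*Protocol article*

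**What the plan says.** Under Study outcome measures the protocol article states: "The primary outcome is changes in 6-min walking distance assessed by the 6-min Walk Test (6MWT) from baseline to the end of the 12-week intervention". Trial oversight also defines the outcome as a change, but over a different interval: "from baseline to 6 months will be served as the primary outcome parameter".

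The Statistical analysis section plans significance tests at baseline: "Comparability of the baseline data between the two groups will be assessed using a two-sample" Student's t test for continuous variables, with chi-square or Wilcoxon tests for categorical ones. On the primary outcome it says: "Analysis of the primary outcome will be conducted according to the intention-to-treat (ITT) principle". It adds imputation for dropouts, a sensitivity analysis for missing data and a general rule that "all tests will be two tailed and a statistical probability of < 0.05 is considered statistically significant". It names no between-group test or model for the primary outcome and no covariate, and it neither states nor excludes adjustment for baseline 6MWT.

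Sample size calculation uses a two-sample formula with no baseline term, where "a superiority one-sided test was employed". Its inputs are group values of 512.5 and 436.2 and an SD of 50.0. They are not labelled as changes.

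**The concern.** Table 2 schedules the 6MWT at baseline, so a strong covariate comes at no extra burden. Read as it stands, the article points towards comparing mean changes without adjustment. A change score subtracts the whole baseline value, which is too much whenever the regression slope of follow-up on baseline is below 1. ANCOVA estimates that slope instead. With equal SDs the slope is r, so the change score is less precise and passes part of any chance baseline difference into the estimate.

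Baseline significance tests do not help with this. Under sound randomisation any baseline difference is due to chance, so the tests address a null already known to be true, and they correct nothing.

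At stake is precision on the primary outcome, and whether the planned 90% power applies to a change when the inputs look like walking distances.

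**Working it through.** **Inputs from the protocol article (Sample size calculation).** Means 512.5 and 436.2, difference 76.3. SD 50.0. Margin 45.0, read as 0.9 × 50. Net difference 76.3 − 45.0 = 31.3. z-values 1.64 and 1.282. Loss to follow-up 20%, so 120 × 0.8 / 2 = 48 per arm.

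**Assumptions.** The correlation r is not given, so a range is used. Baseline and follow-up SDs are taken as equal.

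**1. The plan's own figure.** n = 2 × (1.64 + 1.282)² × 50² / 31.3² = 43.6, so 44 per group. The stated figure is about 49, which these inputs do not reproduce. That is a separate matter. What counts here is that the formula has no baseline term.

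**2. Relative variance.** With σ the SD of 6MWT at one visit:
- change score: 2σ²(1 − r)
- ANCOVA: σ²(1 − r²)
- ratio: (1 + r)/2

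The ratio is 0.65, 0.75, 0.85 and 0.95 at r = 0.3, 0.5, 0.7 and 0.9, giving savings of 35%, 25%, 15% and 5%. It does not depend on what the SD of 50 refers to.

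**3. Cost.** One degree of freedom multiplies the variance by about 1 + 1/(N − 4). At N = 96 this is 1.011. Break-even is at (1 + r)/2 × 1.011 = 1, so r ≈ 0.98.

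**4. Power if 50 is the SD of the 6MWT value.** SE = SD × √(2/48). Power = Φ(31.3/SE − 1.645), the plan's one-sided margin test.

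| r | SD, change | SE | Power, change | SD, ANCOVA | SE | Power, ANCOVA |
|---|---|---|---|---|---|---|
| 0.3 | 59.2 | 12.1 | 83% | 47.7 | 9.7 | 94% |
| 0.5 | 50.0 | 10.2 | 92% | 43.3 | 8.8 | 97% |
| 0.7 | 38.7 | 7.9 | 99% | 35.7 | 7.3 | >99% |

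Change-score power equals 90% when SD = 31.3 / (2.926 × 0.2041) = 52.4. Then 2(1 − r) = (52.4/50)² = 1.098, so r ≈ 0.45.

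**5. Sample size on the same reading** (one-sided 0.05, 90% power), change score against ANCOVA, per arm: 62 against 40 at r = 0.3, 44 against 33 at 0.5, 27 against 23 at 0.7, 9 against 9 at 0.9.

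**6. If 50 is instead the SD of the change,** the change score needs 44 per arm at any r. ANCOVA needs 29, 33, 38 and 42 at r = 0.3, 0.5, 0.7 and 0.9.

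**7. Chance baseline imbalance.** With a baseline SD of 50, the SE of the baseline difference is 50 × √(2/48) = 10.2 m. The expected absolute difference is 10.2 × √(2/π) ≈ 8 m. A difference of 20 m lies 1.96 SEs out and occurs in about 5% of trials. An unadjusted change carries, in expectation, (1 − r) of the imbalance with opposite sign: for 10 m, 5 m at r = 0.5 and 3 m at r = 0.7.

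**The case against.** The strongest reply is that defining the outcome as a change does not commit the trial to an unadjusted analysis. ANCOVA of the change on group and baseline gives the same treatment estimate as ANCOVA of the follow-up value. The model and covariates are often left to a SAP, which is not shown, so their absence from an article is no fault in itself. This stands, and it is why the point is a recommendation.

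It also stands that nothing in the article makes covariate choice or interpretation depend on the baseline tests. They are uninformative but do not bias the primary estimate.

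The power loss is conditional too. It appears only for r below about 0.45 and on the margin test. On a two-tailed test against zero with the planned 76.3 m, even r = 0.3 gives 76.3/12.1 = 6.3 SEs, hence power above 99%.

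Three stronger readings are tempting, and the document supports none of them:
- A reader might infer that baseline data serve only for comparability tests. A change score itself uses baseline 6MWT, and adjustment is not excluded.
- A reader might expect chance imbalances of 10–20 m. Step 7 puts the expected size at about 8 m.
- A reader might take the questionnaire plan, under which scores "will be transformed or analyzed with a nonparametric test", to discard baseline. Either option could be applied to changes, and the sentence does not say.

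**Conclusion.** The point holds as an improvement at negligible cost, not as a demonstrated error. The article defines a change outcome, sizes it without baseline adjustment, plans baseline significance tests and names no primary model. ANCOVA on baseline 6MWT would cut the variance, relative to an unadjusted change, by 35% to 5% as r goes from 0.3 to 0.9, assuming equal SDs. The gain is small if r is high.

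The power figures for the change score (about 83%, 92% and 99% at r = 0.3, 0.5 and 0.7) rest further on reading the SD of 50 as that of walking distance, on 48 per arm, and on the one-sided margin test. The size of the means makes that reading natural, but the article does not state it.

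**What to change.** State the primary analysis as ANCOVA in the ITT set: week-12 6MWT (or its change, which gives the same treatment effect) on group, with baseline 6MWT as covariate. Report the adjusted mean difference with its 95% CI. If the SAP already says this, confirm it there and align the article's wording.

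The 12-week and 6-month definitions of the primary outcome need reconciling first. Table 2 schedules the 6MWT only at baseline and month 3, which fits the 12-week definition.

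Replace the baseline tests with a table of summary statistics by group, without p-values.

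The cost is wording and one degree of freedom. The baseline value is already scheduled, no visit or measurement is added, and SPSS fits the model. The change should be fixed before the database is locked and allocation is revealed to the analysts.

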**Methods/design:**

In this randomized controlled trial, 120 patients will be randomly allocated in a 1:1 ratio to *Baduanjin* exercise combined with conventional exercise of CR (*Baduanjin* exercise group) or conventional exercise of CR alone (conventional exercise group). In addition to conventional physical activity, participants in the *Baduanjin* exercise group will participate in a 45-min *Baduanjin* exercise training session twice a week, for 12 weeks. The primary outcome is walking distance in the 6-min Walk Test (6MWT), and the secondary outcomes are peak oxygen uptake (VO_2_ peak), ventilatory anerobic threshold (VAT), The minute ventilation to carbon dioxide production relationship (VE/VCO_2_ slope), left ventricular end-diastolic volume index (LVEDVi), left ventricular ejection fraction (LVEF), quality of life assessed by the Minnesota Living with Heart Failure Questionnaire (MLHFQ), amino-terminal pro-brain natriuretic peptide (NT-proBNP), hs-CRP, heart rate variability (HRV), New York Heart Association (NYHA) classification, and major adverse cardiovascular events.

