Empirical observations have suggested that *Baduanjin* exercise may improve cardiopulmonary function and exercise tolerance [10–12]. A meta-analysis showed that *Baduanjin* exercise can improve left ventricular ejection fraction (LVEF), cardiac output, stroke output and reduce resting myocardial oxygen consumption in elderly patients. Besides, it can also improve the elasticity of vascular, and regulate blood pressure, glucose, and lipid [13–16]. Compared with conventional exercise, *Baduanjin* exercise can additionally relax and ease the mind and spirit, thus improve sleep quality and unhealthy emotions [17]. These features make *Baduanjin* exercise an optimal exercise for patients with CHF, whose daily activity is greatly limited and who suffered a lot physically and mentally after a long period of medical or surgical treatment. Therefore, *Baduanjin* may be a promising exercise for cardiac rehabilitation for CHF.

However, there is a lack of high-quality evidence for the effectiveness of a *Baduanjin* exercise-based cardiac rehabilitation program for patients with ischemic CHF. Therefore, we conduct this randomized controlled trial (RCT) to evaluate the benefits of a *Baduanjin* exercise-based cardiac rehabilitation program in patients with ischemic CHF. We hypothesized that after the 12-week *Baduanjin* practice, patients would have a greater improvement in cardiopulmonary function, exercise tolerance and health-related quality-of-life scores than those practicing conventional exercise alone.

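### The MLHFQ rule leaves the choice between two methods open, provides for no baseline adjustment and asks for no difference in points; one baseline-adjusted model would settle all three

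*Protocol article*

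**What the plan says.** The Statistical analysis section of the protocol article gives one rule for questionnaires: "Questionnaire score data, known as non-normally distributed data, will be transformed or analyzed with a nonparametric test". MLHFQ is the only questionnaire among the outcomes, and no other section names a method for it. The sentence directly follows the one on baseline comparability, so its use for the outcome is implied rather than stated.

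Other relevant statements:

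- The Background hypothesis is that, after the 12-week practice, "patients would have a greater improvement in cardiopulmonary function, exercise tolerance and health-related quality-of-life scores" than those doing conventional exercise alone.
- Trial oversight states: "Outcomes will be measured at baseline, 3 months and 6 months by researchers blinded to group allocation". It lists MLHFQ among secondary outcomes introduced as changes.
- Table 2 collects MLHFQ at baseline, month 3 and month 6. The 6MWT, cardiopulmonary exercise test, echocardiography, laboratory tests and NYHA class stop at month 3. The MLHFQ paragraph under Study outcome measures gives no visit.
- On testing: "all tests will be two tailed and a statistical probability of < 0.05 is considered statistically significant". On dropouts: "Dropouts will be included in the analysis by modern imputation methods for missing data".
- Randomization and blinding, and Data management, keep the analysts blinded to allocation.

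**The concern.** Quality of life is one of the three benefits named in the trial's aim and hypothesis. For this score the article does not stay silent; it fixes a rule, and the rule is weak in three ways.

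1. It joins two methods with no criterion, and names neither the transformation nor the test. Nothing says that the choice is made before results are seen.
2. It provides for no baseline adjustment, although every patient has a baseline MLHFQ. A two-group test on follow-up scores discards that information.
3. It asks for no effect size. A rank p-value or a difference in transformed means is not a difference in MLHFQ points, while a hypothesis of greater improvement invites the question of how much.

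At stake are the power and readability of the quality-of-life result and, to a smaller degree, its error rate.

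**Working it through.** **No stated figure to reproduce.** The article gives no sample size, power or error rate for MLHFQ, so the check is by simulation and a short formula.

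**Inputs from the article.** 120 patients at 1:1 give 60 per arm. The Sample size calculation says "Assuming conservatively that 20% may be lost to follow-up within 6 months", so 60 × (1 − 0.20) = 48 per arm. Tests are two-sided at 0.05.

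**Assumptions (the article gives no MLHFQ distribution).** Integer scores from 0 to 105, right-skewed (gamma, mean 22, shape 1.5; shape 3 as the less skewed case), latent correlation 0.6 between baseline and month 3, and a 30% reduction in score for power.

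**Error rate, no true effect.** Each test fixed in advance rejects close to 5%: Wilcoxon 5.1%, t test on log scores 5.3%, t test on square-root scores 5.4%. Reporting the smallest of the three p-values at month 3 gives 7.0%; other skewed distributions give 6–7%. A baseline-adjusted model on the raw score holds its size at 4–5%.

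**Is non-normality a reason to leave the points scale?** In a separate null simulation with other assumed skewed scores, a plain t test on untransformed change rejected 5.1% (48 per arm) and 4.4% (60 per arm). At this sample size it is not a compelling reason.

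**Power with a 30% reduction, 48 per arm.**

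| Assumed distribution | Unadjusted rank, log or root test | Baseline-adjusted, original scale |
|---|---|---|
| Strongly skewed (shape 1.5) | about 45–52% | 71% |
| Less skewed (shape 3) | about 79–83% | 95% |

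**Where the gain comes from.** A separate run of 2,500 trials at shape 1.5 gave, unadjusted: Wilcoxon 49%, log 48%, raw t test 55%. Baseline-adjusted: raw 73%, square root 72%, log 65%, ranks 65%. Adjustment therefore helps on every scale, and an adjusted square root does about as well as the adjusted raw score.

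A formula gives the same answer. Adjusting for a baseline with correlation ρ multiplies the standard error by √(1 − ρ²), so

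adjusted power ≈ Φ[(1.96 + z) / √(1 − ρ²) − 1.96], where z is the normal quantile of the unadjusted power.

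With ρ = 0.6, √(1 − 0.36) = 0.8:

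- from 52%: (1.96 + 0.050) / 0.8 − 1.96 = 0.553, power 71%
- from 83%: (1.96 + 0.954) / 0.8 − 1.96 = 1.683, power 95%

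**Range over the assumed correlation**, starting from 52%:

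- ρ = 0.3: 2.010 / √0.91 − 1.96 = 0.147, power 56%
- ρ = 0.8: 2.010 / 0.6 − 1.96 = 1.390, power 92%

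**If the tests are run on change.** Change uses the baseline, but not efficiently. In a simulation with similar assumptions, Wilcoxon on change had 56% power against 52% for Wilcoxon on the follow-up score and 75% for the adjusted raw-scale model.

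**The case against.** The strongest reply is that this is a journal article. The exact test, transformation, covariates and effect measure are details that a full protocol or SAP commonly supplies, and MLHFQ is a secondary outcome. Transformation and rank tests are valid methods, each near 5% error when fixed in advance. The rule does not forbid baseline adjustment, and a Hodges-Lehmann shift would put a rank analysis into points. Analysts are blinded and the database is locked after a blinded check.

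Much of this stands, and it limits the point to a modest one. It does not remove it: the article states a rule, and the rule is an unresolved either/or. Blinding softens the post-hoc choice, but a two-sided p-value can be computed on coded groups.

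Four stronger readings are tempting, and the article does not support them.

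- *Change scores cannot be transformed.* A log or root of a zero or negative change is undefined, but the rule speaks of score data, not change. Scores can be transformed before they are compared or differenced, and sign-tolerant transformations exist.
- *Rank results cannot be pooled over imputed data.* A bare rank p-value has no direct pooling rule, but a Mann-Whitney probability with its variance does. Pooled over 20 imputations with 20% missing, it gave 5.5% type I error. The article also names no multiple imputation, and its imputation sentence sits in a paragraph that opens with the primary outcome.
- *The error rate rises above 10%.* Figures of 10.8% (three tests at two visits) or 12–13% (five versions of the analysis) need more freedom than the text clearly gives. The Background ties the quality-of-life hypothesis to the end of the 12 weeks.
- *Transformation itself costs the power.* The adjusted square-root result shows otherwise.

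**Conclusion.** The point holds in limited form. The MLHFQ rule offers two methods without a criterion, provides for no baseline adjustment and asks for no difference in points. The open choice costs little: about 6–7% instead of 5% at month 3, and only if the most favourable of three tests is always reported. The larger cost is power, roughly 20 percentage points under the strongly skewed assumption (45–52% against 71%) and 12 to 16 under the less skewed one (79–83% against 95%). These sizes rest on assumed distributions, a 30% reduction, 48 per arm and a correlation of 0.6; with a correlation of 0.3 the gain from 52% is only about 4 points. The direction does not depend on the exact values as long as baseline predicts follow-up. It is a worthwhile correction to a secondary outcome and no threat to the primary analysis.

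**What to change.** Replace the questionnaire sentence with one prespecified analysis, for example:

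> *MLHFQ total score is analysed on its original scale in a linear mixed model with months 3 and 6 as responses and baseline score, arm, visit and arm-by-visit as terms. The adjusted difference in points at month 3, with a robust or bootstrap 95% confidence interval, is the quality-of-life result; month 6 is supportive. A rank-based analysis is a sensitivity analysis only.*

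An ANCOVA at month 3 is an acceptable simpler choice, provided that one of the two is named. Month 3 is the end of the 12-week programme and so matches the Background hypothesis. In the mixed model, patients with at least one follow-up score contribute.

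The cost is one sentence, with no new data, since Table 2 already collects all three scores. The small downside is that a skewed score needs a robust or bootstrap interval. The change should be dated and in place before any comparison by arm is seen. If an unpublished SAP already fixes the method, a reference to it would be enough.
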